## Abstract

**Background:** People with Parkinson's disease (PD) experience not only motor problems but also non-motor problems that seriously impede their daily functioning and quality of life. The current pharmacologic treatment of PD is symptomatic, and alternative rehabilitation treatments, which preferably also have a disease-modifying effect and promote neuroplasticity, are needed. Recent studies suggest that high-intensity interval training (HIIT) is promising for promoting neuroplasticity in human PD, with short training time and reduced burden. Biomarkers for neuroplasticity such as brain-derived neurotrophic factor (BDNF) and neurodegeneration (including neurofilament NfL and α-synuclein) may play a role, but their response to HIIT is not well-investigated.

**Objectives:** The aims of this study were (1) to study the effects of 4 weeks of HIIT compared with 4 weeks of continuous aerobic exercise on motor and non-motor outcomes of PD and (2) to investigate the association between HIIT, motor/non-motor performances changes, and blood biomarker levels for neuroplasticity and neurodegeneration.

**Study Design:** Single-subject research design with alternating treatment setup (ABACA) and frequent repeated measurements was used. Each participant received different intervention conditions (B/C) interspersed with baseline periods (A, i.e., ABACA or ACABA), and frequent repeated assessment of outcome measures is done to quantify within-subject, individual response patterns with sufficient power for data analysis. Blood samples were collected once a week in the baseline and training phases (A1 and B/C) and once every 2 weeks in the washout phases (A2 and A3).

**Intervention:** Four subjects with PD on stable dopaminergic medication, two in Hoehn–Yahr stage 1–2, and two in Hoehn–Yahr stage 2.5–3 followed an ABACA or ACABA schedule, consisting of blocks with 30-min sessions of “B” (HIIT) or 50-min sessions of “C” [continuous aerobic exercise (CAE)] 3×/week for 4 weeks, separated by baseline “A” periods of 8 weeks for a total duration of 28 weeks.

**Outcome Measures:** Outcome measures include disease status [Movement Disorder Society-sponsored revision of the Unified Parkinson's Disease Rating Scale (MDS-UPDRS)], blood biomarkers (BDNF, Nfl, and α-synuclein), measures for functional mobility (including an activity tracker), and activities of daily living, as well as cognition, mood, biorhythm (sleeping problems), and quality of life.

**Data Analysis:** Visual analysis of trends in level, slope, and variability in response patterns was carried out, confirmed by longitudinal regression analysis with phase (ABACA) as the independent variable.

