## Methods

### Study Design

We will use a single-subject alternating treatment approach with A1-B-A2-C-A3 or A1-C-A2-B-A3 design to study the effects of HIIT on motor and non-motor performance and neuroplasticity and neurodegeneration biomarkers such that subjects will perform both the HIIT (B-phase) and the moderate CAE training (C-phase) for 4 weeks. After a baseline (A1) period of 4 weeks, the first intervention period of 4 weeks will take place (B or C), followed by a washout period of 8 weeks without an intervention (A2), the second intervention period of 4 weeks (B or C), and finally a third washout period of 8 weeks (A3). Each patient therefore experiences the full set of treatment approaches. The order of interventions B and C will be randomized for each participant (i.e., ABACA or ACABA, two of each, four participants total) using a random sequence generator. Assessment will be done by Good Clinical Practice (GCP)-trained blinded assessors.

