Weekly outcomes are motor performance, namely, the 10-meter walk test (41), the Timed “Up-and-Go” test (TUG) (42), and the one-leg stance test (43). In addition, daily physical activity with a wrist-worn activity tracker will be recorded throughout the study. For weekly self-report outcomes, we will use Ecological Momentary Assessment methodology (44), asking frequent (weekly in baseline phases, three times a week in intervention phases), short online survey questions about non-motor functions using Castor EDC (45): Mood will be assessed with a visual analog scale (VAS) score rating: “Can you rate your current mood on a scale from “1” to “10”?” (a score of “1” represents “very sad”; a score of “10” represents “very happy”). Sleep performance will be assessed with a VAS score rating: “Can you rate how well you slept last night on a scale from “1” to “10”?” (A score of “1” represents “very bad”; a score of “10” represents “very good”). Cognitive function will be assessed with a VAS score for “ability to concentrate”: “Can you rate well you are able to concentrate on daily tasks on a scale from “1” to “10”?” (a score of “1” represents “very bad”; a score of “10” represents “very good”). In addition, we will ask the subjects to keep a logbook of their attended sessions and perceived effort (RPE).

Blood samples (for serum BDNF, NfL, and α-synuclein) will be collected by a trained nurse once a week in the baseline and training phases (A1 and B/C). Blood draw frequency is decreased to once every 2 weeks in the washout phases (A2 and A3) to reduce patient burden. Twenty-milliliter blood samples will be taken from the antecubital vein at rest in the morning hours between 08:00 and 10:00 in the fasting state. We will use anticoagulant-free tubes, which be placed on ice (−80°C) until further analysis. BDNF concentration will be measured with a commercially available and in-house validated kit (Quanterix Simoa). Serum NfL and α-synuclein concentrations will be measured using an in-house developed Homebrew Simoa assay (17, 46).

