**Figure 1 F1:**
[figure not shown]
Intensity-work rate plot for CAE and HIIT session. **Left:** intensity-work rate plot for a 50-min CAE intervention session. **Right:** intensity-work rate plot for a 30-min HIIT intervention session. CAE training intensity will be at about 55% W-max, HIIT will alternate between training intensity 35% W-max during low-intensity intervals and >85% W-max at high-intensity intervals. CAE, continuous aerobic exercise; HIIT, high-intensity interval training.

Each HIIT session is about 30 min of interval training, starting with a 5 min of warm-up at 25–35% W-max. Subsequently, six to eight blocks of HIIT will be performed, alternating 45 s at >85% VO_2_-max, with 90 s at 30–40% W-max. After the interval block, 5 min of cooling-down will be performed at 20–35% W-max. Workload will be progressively adapted using a fixed weekly schedule or upon therapist decision by adding intervals at the end of the sessions.

Each CAE session is about 50 min of continuous training at a preset workload of about 55% W-max. Workload will be progressively adapted after every week by reducing rest time, based on a fixed schedule or upon therapist decision. A trained physiotherapist-supervisor, assisted by GCP-trained interns from the Faculty of Human Movement Sciences will assist the subjects with water, music, and motivational encouragements. Throughout the study, patients are asked to maintain their regular medication.

The Ecological Momentary Assessments taken weekly (A phases) or every other day (B/C phases) using the online survey throughout the study period will act automatically as reminders and will help with compliance to training and assessments. We will comply with consensus recommendations of Slade et al. (47) regarding reporting on exercise interventions.

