### Statistical Analysis

Although the protocol specifies primary and secondary study outcomes, we will assess the results based on a combination of those parameters.

For example, the primary research parameter that we have specified is the MDS-UPDRS-III, which is measured before and after each phase. If, under the influence of the interventions, there are improvements within the participants that are greater than the measurement error of 3.25 points known from the literature (48), this is a clear indication that the intervention influences motor function. However, if there is less or no change in the MDS-UPDRS-III but in one or more other parameters, this is still informative with regard to the effects of the different interventions and the underlying mechanisms. If no change is visible in any parameter under the influence of the interventions in any participant (through visual analysis and/or statistical tests), then the conclusion should be that there is no effect.

Visual inspection is the method of choice for single-subject research designs (SSRDs) (24). We will inspect, analyze, and describe the changes across the baseline and intervention phases (phase mean level and data spread), and we will compare the trend (slope) of scores with the baseline mean levels and variability (standard deviations) on outcomes for each intervention strategy and each patient. Longitudinal regression analysis with “phase” (i.e., condition) as the independent variable will be used for further confirmation (α = 0.05).

We will not explicitly test for group differences between patients in Hoehn–Yahr stage 1–2 or for patients in Hoehn–Yahr stage 2.5–3, but we will get insights on the direction of effects and effect sizes in the intervention phases compared with the baseline phases, which we will report descriptively for both participants in both subgroups.

The association between biomarkers and symptom changes will be quantified by Pearson correlation coefficients and corrected for age, between changes in BDNF, α-synuclein, and Nfl and change scores on primary and secondary parameters.

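### The phase regression named as confirming level, slope and variability compares phase means only, so it cannot confirm a slope, and with the Table 1 visit labels it dilutes a gradual training effect

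*Protocol article*

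**What the plan says.** The abstract's Data Analysis paragraph reads: "Visual analysis of trends in level, slope, and variability in response patterns was carried out, confirmed by longitudinal regression analysis with phase (ABACA"), with phase as the independent variable. The Statistical Analysis section makes visual inspection the main method. Under it, phase level and spread are described and "we will compare the trend (slope) of scores with the baseline mean levels and variability (standard deviations) on outcomes". It then adds: "Longitudinal regression analysis with “phase” (i.e., condition) as the independent variable will be used for further confirmation (α = 0.05"). Neither place names a time term, a phase-by-time term or a model for the variance.

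Training blocks last four weeks and are progressive. For HIIT the Training Protocol says: "Workload will be progressively adapted using a fixed weekly schedule" or at the therapist's decision.

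Table 1 fixes the reading times. Inside each B or C block:
- Blood markers, 10 m walk and one-leg stance are marked at session s1 of weeks 1 to 4.
- The VAS items are marked at all twelve sessions.
- MDS-UPDRS and TUG are marked once, at week 1 s1. Their next reading is week 1 s1 of the following A phase.

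**The concern.** The plan names three features to look for and one model to confirm them. A regression on phase alone has a coefficient for each phase mean and nothing else, so slope and variability have no counterpart in it.

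This matters because a training response may well build up over the block, which would show as a slope. The in-block visits carry 0 to 3 weeks of training, and the visit after the full four weeks carries a washout label. A phase contrast then averages a partial build-up and assigns the most informative reading to the comparator side. This happens without any disease drift. At stake are whether a visible gradual response gets statistical support, and the size of the HIIT and CAE effects passed on to later trials.

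**Working it through.** **Inputs from the protocol**
- Block length, Study Design: "the first intervention period of 4 weeks will take place (B or C").
- Blood, Outcome Measures: serum samples "will be collected by a trained nurse once a week in the baseline and training phases (A1 and B/C"). Table 1 places them at s1, so after 0, 1, 2 and 3 weeks of the block.
- Motor tests, Outcome Measures: "Weekly outcomes are motor performance, namely, the 10-meter walk test (41"). Table 1 has the 10 m walk and one-leg stance at the same four times. The text also calls TUG weekly, but Table 1 marks it once per block.
- VAS: three readings a week on the Monday, Wednesday and Friday training days, so 0, 2/7 and 4/7 of a week after each week's start.

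**Assumptions, not in the protocol:** flat A1, and an effect rising linearly from 0 at block start to D at 4 weeks. The plan gives no expected effect or power, so there is no figure of its own to reproduce.

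**1. What the model estimates.** With phase as the only term, the coefficient is mean(B) − mean(A1). Suppose the in-block values are −1.5, −0.5, 0.5 and 1.5 units around the baseline mean. The slope is clear, yet the contrast is (−1.5 − 0.5 + 0.5 + 1.5)/4 − 0 = 0.

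**2. Weekly outcomes against A1.** (0 + 1/4 + 2/4 + 3/4)/4 = 0.375 D.

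**3. Other shapes and timings, weekly outcomes**

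| Assumption | Phase contrast |
|---|---|
| Quadratic build-up: (0 + 1 + 4 + 9)/16/4 | 0.22 D |
| Saturating, time constant 2 weeks | 0.52 D |
| Saturating, time constant 1 week | 0.62 D |
| Linear, read at end of week: (1 + 2 + 3 + 4)/4/4 | 0.625 D |

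**4. VAS items.** The mean reading time is 1.5 + 2/7 = 1.786 weeks, and 1.786/4 = 0.446 D.

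**5. MDS-UPDRS-III and TUG.** The one in-block reading is at time 0. The contrast with the preceding A phase is 0 − 0 = 0 D, and any gain appears under the next A label.

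**6. If phase is read as condition and all A readings are pooled** (weekly outcomes, first block, 4 + 4 + 5 = 13 A readings):
- No retention: 0.375 D.
- Linear loss over 8 weeks: A2 carries 1 + 0.75 + 0.5 + 0.25 = 2.5, so 0.375 − 2.5/13 = 0.18 D.
- Full retention: 0.375 − 9/13 = −0.32 D.

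**7. Effect of re-aligning and adding a slope.** Treat week 1 s1 as pre-training (five pre-training readings) and the first visit after the block as end of training (four readings, at 1, 2, 3 and 4 weeks). With σ the within-person SD and independent errors:

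| Estimate | Recovers | Standard error | Ratio, in D/σ |
|---|---|---|---|
| Phase means as labelled | 0.375 D | √(1/4 + 1/4) = 0.71σ | 0.53 |
| Phase means, aligned | 0.625 D | √(1/5 + 1/4) = 0.67σ | 0.93 |
| Fitted value at 4 weeks minus pre-training mean | 1.00 D | √(1/5 + 1/4 + 1.5²/5) = 0.95σ | 1.05 |
| Fitted value at 4 weeks minus extrapolated pre-training line | 1.00 D | √(1/5 + 6²/10 + 1/4 + 1.5²/5) = 2.12σ | 0.47 |

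**8. Power, illustration only.** For D = 3σ, two-sided 0.05, simulation gives 16% for phase means as labelled and 53% for aligned phase means. The value 3σ is arbitrary.

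**The case against.** **The article never says phase is the only term.** A time term could sit in a full protocol or SAP that is not shown, and model detail is commonly left there. That is fair, but the article does name the model and says what it confirms, and as named the two do not match. A reader might infer that the plan rules out a time term; it does not.

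**Visual inspection comes first.** The regression "as the independent variable will be used for further confirmation", and a conclusion of no effect requires that nothing is visible in any parameter in any participant. A reader might therefore infer that a gradual response would be thrown out for missing α = 0.05. The text does not support that: such a response would go unconfirmed, not be discarded. The study is also an exploratory pilot in four people.

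**The 3/8 is not general.** This stands. It needs a linear rise, no gain at the first reading and a flat comparator, and the protocol states no effect shape. Progressive workload describes the training dose, not the response. A response complete within a week would give (0 + 1 + 1 + 1)/4 = 0.75 D.

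**The primary outcome may already be handled.** The Statistical Analysis section describes MDS-UPDRS-III as taken around each phase and judged against a 3.25-point measurement error, which reads as a pre–post comparison. So one cannot infer that the study is blind to a change in it. The problem is limited to a regression that uses the Table 1 phase labels.

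**A single build-up term is not an obvious replacement.** A term equal to the share of training completed would fix one assumed shape, has no defined value at later washout visits, and picks up drift. At 0.1 SD per week with no training effect it reports 0.64 SD, against 0.40 SD for the labelled phase means. Part of any gain over the labelled model comes from visit alignment alone, as step 7 shows.

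**Conclusion.** The point holds in a limited form. As named, the confirming regression tests level and cannot confirm slope or variability; this follows from the text without any assumption about effect size. Dilution of a gradual effect also follows from the visit times and labels, but its size depends on the assumed shape. For weekly outcomes against A1 it is 0.375 D if linear and about 0.22 to 0.63 D across the other shapes and timings tried. The VAS items give 0.45 D under the linear shape. For MDS-UPDRS-III and TUG, a contrast by phase label against the preceding A phase gives 0 for any effect that starts from zero at the beginning of the block. The consequence is missing confirmation and understated end-of-training effects, not a wrong overall conclusion. It is worth correcting because the change is cheap.

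**What to change.** - **Weekly and VAS outcomes:** add time-in-phase and phase-by-time terms to the confirming regression. Treat the week 1 s1 reading of each block as pre-training and the first visit after the block as the end-of-training reading. Report the fitted end-of-training effect for HIIT and for CAE beside the phase-mean contrast. State the comparator: the pre-training mean matches the plan's own comparison with baseline level and is far more precise than an extrapolated baseline line (0.95σ against 2.12σ), but it does not remove drift, so report the baseline slope with it.
- **MDS-UPDRS-III and TUG:** define the contrast by pre-block and post-block visit, not by phase label. Reconcile the text and Table 1 on whether TUG is weekly in the training blocks; if it is, it joins the first group.
- **Variability:** state that changes in spread are descriptive and are not confirmed by the regression.
- **Second analysis:** keep the phase-mean model.

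The cost is wording and analysis time; apart from the TUG reconciliation, no visit or sample changes. The extra terms use degrees of freedom with few readings per person and raise the standard error (0.95σ against 0.71σ for the labelled phase means), which is the reason to keep the simpler model alongside.

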## Introduction

Parkinson's disease (PD) is a complex, chronic, highly disabling progressive neurodegenerative movement disorder, characterized by the loss of dopamine neurons in the substantia nigra (1). The disease is characterized by motor (e.g., tremor, gait disturbance, bradykinesia, and falls) and also non-motor (e.g., depression, reduced cognitive performance, and biorhythm/sleep) symptoms (2). To date, there is no cure. Current treatment paradigms are mainly aimed at alleviating motor and psychiatric features but do not consider individual differences in treatment response or molecular profile. Moreover, several motor (e.g., gait disturbances and balance disturbances) and non-motor (e.g., mood disturbances, cognitive functioning, and sleep problems) features respond insufficiently to current pharmacological treatments; and unfortunately, we do not have rehabilitative strategies that halt or slow down disease progression (2, 3). Frequent physical exercise training is increasingly recognized as an effective therapy for PD and other neurodegenerative diseases that may even exert disease-modifying influences through neuroplastic mechanisms (4, 5).

Aerobic and/or progressive resistance exercise based on the American College of Sports Medicine recommendation of 3×/week, 30–60 min/session for at least 12 weeks demonstrate long-term (>12 weeks) improvements in both motor performance [e.g., walking speed, aerobic capacity, and lower-limb muscle strength; (6)] and cognitive performance (attention and executive functioning) in PD patients (3, 7). Shorter-lasting aerobic exercise programs (3×/week, 30–60 min/session for 4 weeks) may also show improvements in motor performance (e.g., walking speed and aerobic capacity), though the long-term effects of short-term aerobic exercise are less consistent (4).

Physical training studies show promising results in terms of exercise-induced neuroplasticity, at both symptom and molecular levels in human and animal models of exercise and PD (8). For example, voluntary treadmill running in mice for 40 min/day, 5 days/week for 18 weeks improved motor coordination and aerobic capacity and reduced nigrostriatal neuronal loss (9). The improvements were associated with increased levels of BDNF in the substantia nigra and striatum. A recent review and a meta-analysis showed that HIIT has acute and long-term effects on serum BDNF levels (10, 11). Several studies suggest that serum BDNF concentration levels are reduced in PD patients [for example, Frazzitta et al. (12)]. Low BDNF is associated not only with cognitive impairments in PD patients (13) but also with mood disturbances (14). Biomarkers for neuroplasticity, such as BDNF, and biomarkers for (synaptic) neurodegeneration (including neurofilament NfL and α-synuclein) are, respectively, decreased and increased in PD patients compared with age-matched controls (15–17). Studies suggest intensive physical training to be promising for modulating these biomarkers in people with PD (11, 12). BDNF has shown to respond well to intensive physical training; for serum NfL and α-synuclein, this has not yet been properly investigated.

A promising, time-efficient, and highly effective physical exercise strategy is “high-intensity interval training” (HIIT), which only recently is being explored in clinical research (18). HIIT encompasses several intervals of short-lasting, high-intensity bouts alternated with low-intensity bouts, that has shown to match or even surpass the cardiovascular responses to moderate continuous aerobic exercise (CAE) (19). This increased efficiency is achieved in a shorter period of total training time, which may enhance the motivation of PD patients and help promote adopting a more active lifestyle (19). For example, HIIT for three 40-min sessions per week for 8 weeks has been suggested to evoke enhanced adaptive aerobic capacity (e.g., increased aerobic capacity) as well as increased cognitive performance, as compared with CAE in healthy older adults and older adults with mild cognitive impairment (19). Similar results have been found for adult type 2 diabetes mellitus patients (18) and adult cardiovascular patients (4).

Only a few studies to date have investigated the effect of HIIT on motor and non-motor outcomes in PD. High feasibility of HIIT in PD was recently demonstrated (20): participants were able to be complete 45 min of HIIT three times a week for 12 weeks without intervention-related dropouts and >80% compliance. Group session HIIT consisted of an exercise gym circuit designed to elicit a physiological response indicative of high-intensity exercise (≥85% HRmax). Fernandes et al. (21) performed a pilot randomized controlled single-blind trial to study the effect of 12 weeks of HIIT vs. moderate-intensity continuous exercise (MICE) training in PD. They enrolled 20 participants, with Hoehn–Yahr stage 1–3, who performed walking/jogging training three times per week for 12 weeks. The HIIT protocol consisted of a 1-min walking/jogging bout at rating of perceived exertion (Borg scale RPE) scale 15–17 level alternated with 2 min of walking at 9–11 level of RPE during a 25-min session. MICE training consisted of 26 min of walking/jogging at 11–14 level of RPE. HIIT improved 6-min walk test distance and increased endothelial reactivity (a marker for increased blood flow). These values did not change with MICE. They did not measure non-motor outcomes. O'Callaghan et al. (22) entered the sample by Harvey et al. into a new comparison in a 12-week pilot study of HIIT or MICE. Their study supports the feasibility of HIIT in PD and found that HIIT increased circulating serum brain-derived neurotrophic factor (BDNF), a protein that may play a key role in neuroplasticity maintaining or improving brain functions (10). BDNF levels were higher after HIIT compared with continuous moderate-intensity aerobic training (22).

The combined evidence of animal and human studies suggests that motor performance, cognitive performance, and mood in PD are related and that biomarkers for neuroplasticity and neurodegeneration are associated with both motor and non-motor features. This underpins the importance of disease-modifying treatment in PD including aerobic and/or progressive resistance exercise as adjuncts to pharmacological treatment for the control of motor and non-motor features. As such, determining the optimal type and dosage of exercise interventions to obtain these neuroplastic effects is an important focus of current neurorehabilitation research in PD (8, 23).

Researchers argue that the heterogeneity of patient populations and use of classic intervention study design are major confounding factors in making progress toward determining optimal type and dosage of exercise interventions (24). Within-participant research designs with frequently repeated measurements (i.e., single case experimental designs) may be more suitable than group studies to capture individual recovery patterns. This design allows for more continuous repeated measures of the target outcomes, at baseline, during, and after the intervention period (25). Incorporation of many repeated measures allows a detailed analysis of individual responses with adequate power. No single study has compared the effects of HIIT with CAE on changes in motor performance, cognitive abilities, mood disturbances, and biorhythms/sleep in people with PD and whether improvements are associated with quantitative changes in blood-based biomarkers (BDNF, NfL, and α-synuclein).

Therefore, the first objective of this pilot study is to explore the response patterns of motor and non-motor performance and serum biomarker levels to 4 weeks of HIIT compared with 4 weeks of traditional moderate CAE in four single subjects with PD. The second objective is to explore the associations between changes in motor and non-motor outcome measures and serum neuroplasticity and neurodegeneration biomarkers for both exercise conditions.

Our central hypothesis is that HIIT is more effective at improving motor performance, cognition, mood, and sleep as well as increasing concentration of BDNF and decreasing NfL and α-synuclein levels than moderate-intensity CAE. In addition, we expect that HIIT-induced changes in serum BDNF, NfL, and α-synuclein protein levels are associated with changes in motor and non-motor performance of PD patients.

